#### Treatment integrity

*On the road to recovery* will be given by licensed cognitive behavioral therapists. All therapists are experienced in working with the F2F CBT protocol for severe fatigue in cancer survivors. They will participate in a weekly supervision, in which cases are discussed in the presence of senior clinical psychologists (HK, TB). Changes in individual treatment plans will be made according to the study protocol and to the CBT principles for severely fatigued cancer survivors.

At the end of the study, a random 5 % of the e-mail messages send to the patients will be evaluated. An experienced clinician (HK) and researcher (HA) will determine whether the web-based CBT was delivered according to the predefined treatment protocol. To determine if web-based CBT is less time consuming than F2F CBT, therapists will register the invested time for each patient.

#### Control condition: care as usual

Participants in the control condition will be on a waiting list for regular F2F CBT for fatigue in cancer survivors. The total duration of the waiting list is 6 months. In this period, patients will receive care as usual. The usual care for breast cancer survivors in the Netherlands consists of follow-up examinations conform the Dutch guidelines for oncology care [47]. The frequency of these follow-up examinations depends on age, time since diagnosis and a possible BRCA1/2 mutation. In general, there will be a 3-month follow-up in the first year, a biannual follow-up in the second year, and an annual follow-up in the following years up to 5 years after diagnosis.

Recently, a guideline for the management of psychosocial distress in breast cancer survivors is implemented [48]. According to this guideline, psychosocial problems are identified and patients should be referred to specialized care providers. Participants may therefore be referred to other fatigue-oriented interventions during the study (e.g. psychosocial interventions, a rehabilitation trajectory, or physical therapy). At T1, all participants will be asked if they have received any treatment for fatigue during the study, and if so, they are asked to describe this treatment.

### Outcomes

#### Primary outcome

*Fatigue severity*, measured by the subscale Fatigue Severity (8 items, 7-point Likert Scale) of the Checklist Individual Strength (CIS) [49]. This subscale consists of eight items, scored on a 7-point Likert scale. The range of scores is 8 to 56, with a higher score indicating a higher level of fatigue. The cut-off score for severe fatigue is ≥35 [49]. The CIS has been established as a valid and reliable measure [50, 51], which showed sensitivity to detect change in previous studies investigating fatigue in cancer survivors [22, 33, 52, 53].

#### Secondary outcomes

*Functional impairments,* measured by the Sickness Impact Profile 8 (SIP) [54, 55]. This questionnaire addresses the level of disability in eight domains: alertness behavior, sleep/ rest, homemaking, leisure activities, mobility, social interactions, ambulation, and work. The weighted total score on these eight domains will be used to assess functional disability, with higher scores indicating more disabilities. The SIP is a reliable measure with sufficient content validity [56].

*Psychological distress*, measured by the total score on the Brief Symptom Inventory 18 (BSI-18) [57]. This multidimensional questionnaire consists of 18 items, scored on a 5-point Likert scale. The range of scores is 0 to 72, with a higher score indicating more psychological distress. The BSI-18 is a shortened version of the Symptom Checklist 90 (SCL-90) [58]. The BSI-18 has high levels of sensitivity and specificity [59].

*Quality of life*, measured by the European Organization for Research and Treatment of Cancer Quality of Life Questionnaire Core 30 (EORTC-QLQ-C30) [60]. This questionnaire consists of 30 items that cover five function scales (physical, role, cognitive, emotional and social functioning), three symptom scales (fatigue, pain, and nausea and vomiting), and a global health and quality of life scale. All scales are scored on a 4-point Likert scale. The EORTC-QLQ-C30 has been established as a valid and reliable measure [61].

#### Other variables

Demographic variables will be assessed by using a self-report questionnaire at T0. The instruments used to determine the relevant fatigue-perpetuating factors are shown in Table 2.

### Power

The sample size calculation is based on the guidelines of Borm et al. for analysis of covariance (ANCOVA) in RCT’s [72]. A clinically relevant difference of six points is expected for the primary outcome (fatigue severity subscale of the CIS) between the intervention and control condition. This difference is based on a study of Knoop et al. [73], in which the efficacy of a minimal intervention for patients with chronic fatigue syndrome was examined [73]. A minimum number of 60 patients per condition would be needed for a *t*-test with an alpha of 0.05, a two-sided significance level and a power of 0.85. According to Borm et al. [72], this number of patients needs to be multiplied by a “design factor” to calculate the needed sample size for an ANCOVA [76]. This factor is one minus the squared correlation coefficient between the baseline and outcome measure of fatigue severity. In our previous study examining the efficacy of F2F CBT for fatigue in cancer survivors, the correlation of the baseline and outcome measure was 0.36 [22, 33]. This leads to a factor of 0.87 (1 - .36^2^ = 0.87). Thus, the minimal number of patients in each condition is 53 (60*0.87 = 52.2) . The drop-out rate in our first RCT examining F2F CBT for fatigue in cancer survivors was 13 % [22, 33]. In the current study, patients might experience less support from their therapist in the web-based CBT. Therefore, the drop-out in the current RCT is estimated to be 50 % higher than in the first RCT (1,5*13 = 19,5 %) Therefore, a margin of 19,5 % for drop-out is added to the minimal number of 53 patients per condition. This results in a sample size of 132 severely fatigued breast cancer survivors.

### Intended statistical analyses

The primary objective of the study is to examine the effects of web-based CBT on reducing fatigue severity compared to care as usual. Therefore, an analysis of covariance (ANCOVA) will be used with the CIS-fatigue score at T1 as dependent variable, the CIS-fatigue score at T0 as covariate and condition as fixed factor [39]. The clinical importance of the treatment effect will be determined. Differences between the intervention and control condition on the amount of change in fatigue severity will be calculated on T0 and T1. Clinically meaningful change will be defined as a reliable change index of more than 1.96 and a decrease of the fatigue level to a normal range (i.e. a score of <35 on the fatigue severity subscale of the Checklist Individual Strength). The effects of web-based CBT on the secondary outcomes of the study (functional impairments, psychological distress and quality of life) compared to care as usual will be determined with ANCOVA’s. For each secondary outcome measure, an ANCOVA will be performed with the score of the outcome measure at T1 as dependent variable, the score at T0 as covariate and condition as fixed factor. The third objective of the study is to examine if time since completion of cancer treatment moderates the effects of web-based CBT. This will be analyzed with an ANCOVA with time since completion of cancer treatment (3 months-1 year versus ≥1 year) as covariate. The CIS-fatigue score at T1 will be the dependent variable, and the fatigue score at T0 will be the second covariate. All data analyses will be based on intention to treat. Missing values on primary and secondary outcome measures will be replaced with multiple imputation using fully conditional specification with at least five imputations. In case of statistically significant differences, a sensitivity analysis will be performed, based on different assumptions about the values of missing data.

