### Randomization

Stratified randomization will be based on time since completion of cancer treatment (3 months up to 1 year versus ≥ 1 year) and type of referral (referrals by medical professionals versus self-referrals). After T0, randomization will be performed by a test assistant in the presence of the patient. A computerized randomization tool, built by an independent statistical expert, will be used to randomly allocate patients to either intervention or control condition. The allocation ratio will be 1:1 and block-randomization will be used with a block size of six. The test assistant, the researcher and the participants will be blinded to the allocation sequence. They will not be blinded for the randomization outcome, because this is not possible in psychological treatments.

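### The primary and secondary ANCOVAs omit both randomisation stratification factors; if these factors are prognostic, the tests are conservative and some power is lost

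*Protocol article*

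**What the plan says.** Under Randomization, the protocol article states: "Stratified randomization will be based on time since completion of cancer treatment", split at one year. The second stratification factor is whether the patient was referred by a medical professional or referred herself. On the mechanics it says: "The allocation ratio will be 1:1 and block-randomization will be used with a block size of six".

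Under Intended statistical analyses, the primary model has CIS-fatigue at T1 as dependent variable, with "the CIS-fatigue score at T0 as covariate and condition as fixed factor". Each secondary outcome gets the same form: "the score at T0 as covariate and condition as fixed factor". Neither model contains a stratification factor.

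Time since treatment does enter one analysis of CIS-fatigue, the one for the third objective: "This will be analyzed with an ANCOVA with time since completion of cancer treatment". Referral type enters no analysis in the article.

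**The concern.** Blocked randomisation within strata makes the arms nearly equal in their mix of strata. Any difference in outcome between strata then largely drops out of the true sampling variation of the treatment difference. A model without the strata does not register this and still counts the between-stratum variation as residual error. If the strata predict the outcome, the reported standard error therefore exceeds the true one. The test rejects less often than 5% under the null, the confidence interval is wider than it needs to be, and the chance of detecting a real effect is somewhat lower than it could be.

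The article names the dependent variable, covariate and fixed factor for the primary and secondary analyses. The omission is therefore a choice fixed in the text and not a detail left to a fuller plan.

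**Working it through.** **Inputs from the Power section.** "A clinically relevant difference of six points is expected for the primary outcome"; the t-test calculation uses "an alpha of 0.05, a two-sided significance level and a power of 0.85" and gives 60 per condition. The baseline-outcome correlation is 0.36 and drop-out is 19.5%. The SD is not stated.

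**Reproducing the sample size.** The design factor is 1 − 0.36² = 0.8704, and 60 × 0.8704 = 52.2, rounded up to 53 per arm. Then 53 / (1 − 0.195) = 65.8, rounded up to 66 per arm, or 132 in total. The stated figure reproduces.

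**Implied SD.** Solving for the SD at which 60 per arm gives 85% power for 6 points gives 10.97 by the normal approximation and 10.88 by the t distribution. Taking 10.88, the residual SD after baseline adjustment is 10.88 × √0.8704 = 10.15. The planned model's standard error at 53 per arm is 10.15 × √(2/53) = 1.972.

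**Assumption.** Let R² be the share of that residual variance explained by the two strata together. The documents give no value, so 0, 2%, 5% and 10% are shown.

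**Formulas.** With the arms balanced within strata, the true standard error is 1.972 × √(1 − R²), while the planned model still reports about 1.972. Critical values are 1.983 on 103 df (planned) and 1.984 on 101 df (adjusted).

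- Type I error, planned test: 2 × [1 − Φ(1.96 / √(1 − R²))]
- Power, planned test: Φ[(6 − 1.983 × 1.972) / (1.972 × √(1 − R²))]
- Power, adjusted test: Φ[6 / (1.972 × √(1 − R²)) − 1.984]

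| R² | True SE | Type I error, planned | Power, planned | Power, adjusted | Gain (points) |
|---|---|---|---|---|---|
| 0 | 1.972 | 5.0% | 85.5% | 85.5% | 0 |
| 2% | 1.952 | 4.8% | 85.8% | 86.2% | 0.4 |
| 5% | 1.922 | 4.4% | 86.2% | 87.3% | 1.1 |
| 10% | 1.871 | 3.9% | 86.8% | 89.0% | 2.1 |

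Gains are taken before rounding. Planned power also rises with R², because stratification reduces the sampling variation of the unadjusted estimate too. Holding it at 85.5% in every row would overstate the benefit of adjustment.

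**Simulation check.** The set-up was 132 patients, permuted blocks of six in four strata, 19.5% random drop-out, both factors split 50/50 (assumed) and 6,000 runs per setting. It used the normal-approximation SD of 10.97.

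- R² = 5%: type I error 4.5% planned and 4.9% adjusted; power 84.7% and 86.0%.
- R² = 10%: type I error 3.9% planned and 4.9% adjusted; power 85.9% and 88.1%.
- R² = 0: power 84.6% planned and 84.3% adjusted, equal within simulation error.

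The simulated gains of 1.3 and 2.2 points agree with the table.

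**The case against.** The strongest objection is that nothing in the article shows that either factor is prognostic. The Randomization section gives no reason for stratifying. The background section on the right time to intervene, together with the third aim, suggests that time was chosen because it might moderate the treatment effect, which is not the same as predicting outcome. The same section reports that fatigue stops falling about three months after treatment, which points to a weak main effect of time. On referral type and outcome the article is silent. This objection stands, and it makes the consequence conditional.

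The 10% scenario is also demanding. A single 50/50 factor would need a gap between its levels of 2 × 10.15 × √0.10 = 6.4 points, more than the 6-point treatment effect. Shared equally between two such factors, each needs 2 × 10.15 × √0.05 = 4.5 points.

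Further, the trial was sized for the very ANCOVA that is written, and that model reaches the planned 85% power without the strata.

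A reader might infer that stratifying proves the factors matter, or that leaving them out throws away what stratification gained. The documents support neither. No prognostic claim is made, and the unadjusted estimate keeps its reduced sampling variation. Only the reported standard error fails to show it.

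What survives is that the omission is explicit, its direction is known, and adding the terms costs almost nothing even if they prove uninformative.

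**Conclusion.** The point holds as a conditional, modest loss of efficiency. That both factors are missing from the primary and secondary models is certain from the text. That this makes the tests conservative depends on the factors predicting the T1 outcome after adjustment for T0, which the documents do not establish. Over an assumed 2% to 10% of residual variance, the loss is about 0.4 to 2.1 power points; with no prognostic value there is none. The power figures also rest on an SD back-calculated from the Power section and on near-balance within strata; they refer to CIS-fatigue only, although the direction is the same for the secondary outcomes.

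It would be wrong to conclude that the primary analysis is invalid or the trial underpowered. The treatment estimate is unbiased, the type I error does not exceed its nominal level, and 132 remains correct for the stated inputs.

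**What to change.** Write the primary model as CIS-fatigue at T1 on CIS-fatigue at T0, condition, time stratum (3 months up to 1 year versus 1 year or more) and referral type, with the last two as fixed factors. Add the same two terms to each secondary ANCOVA.

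Both variables must be known before a patient can be randomised, so they bring no missing data. The cost is two degrees of freedom (103 to 101 at 53 per arm) and a change of wording. Sample size and data collection stay as they are.

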### Aims of the CHANGE study

To examine the efficacy of web-based CBT for severely fatigued breast cancer survivors on fatigue severity compared to care as usual.To examine the efficacy of web-based CBT for severely fatigued breast cancer survivors on functional impairments, psychological distress, and quality of life compared to care as usual.To examine if time since completion of cancer treatment moderates the efficacy of web-based CBT with respect to fatigue severity.

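### The model stated for the moderation aim has no condition-by-time interaction, so it cannot test whether the effect of web-based CBT depends on time since treatment

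*Protocol article*

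**What the plan says.** The article lists three aims. The third reads: "To examine if time since completion of cancer treatment moderates the efficacy of web-based CBT with respect to fatigue severity". The section on intended statistical analyses repeats it: "The third objective of the study is to examine if time since completion of cancer treatment moderates the effects of web-based CBT".

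The analysis then given for this aim is: "This will be analyzed with an ANCOVA with time since completion of cancer treatment (3 months-1 year versus ≥1 year) as covariate". The next sentence completes the model: "The CIS-fatigue score at T1 will be the dependent variable, and the fatigue score at T0 will be the second covariate".

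The model therefore has one outcome (CIS-fatigue at T1) and two named covariates (time stratum and CIS-fatigue at T0). No product term, stratum-specific treatment effect or other contrast of treatment effects is named there or elsewhere in the article. Condition is not named in this model either. The primary model in the same section does name it, with "the CIS-fatigue score at T0 as covariate and condition as fixed factor", and so does the model for the secondary outcomes.

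Time since treatment, with the same cut at 1 year, is also one of the two stratification factors in the Randomization section.

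**The concern.** Moderation means that the difference between conditions is not the same in the two time strata. A model with time stratum only as a covariate has no parameter for that. Its time coefficient compares fatigue at T1 between early and late survivors, whatever treatment they had.

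Followed as written, the analysis can go wrong in two ways. It can suggest moderation when time since treatment is merely prognostic, and it can miss moderation that is real. The section on the right time to intervene presents the offer of CBT from 3 months, where the group's earlier trials waited at least 1 year, as a way to examine whether earlier treatment is possible. This is the only stated analysis that would compare efficacy by timing.

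**Working it through.** **Reproducing the plan's own figure.** The sample size is built for the main effect; none is given for the third aim.
- Design factor: 1 − 0.36² = 0.8704.
- 60 × 0.8704 = 52.2, taken as 53 per condition.
- 53 / (1 − 0.195) = 65.8, so 66 per condition and 132 in total. This matches the Power section.

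**Inputs.**
- Difference of 6 points; 60 per condition; two-sided alpha 0.05; power 0.85; baseline-outcome correlation 0.36 (Power section).
- SD: not stated. Solving the *t*-test calculation backwards gives about 10.9. The normal formula gives 6 / [√(2/60) × (1.960 + 1.036)] = 10.97, and the *t*-test version 10.88.
- Residual SD after baseline adjustment: 10.88 × √0.8704 = 10.15.
- Split between time strata: not stated, so assumed and varied.

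**What the time coefficient estimates.** Let the true model be

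T1 = α + β·T0 + τ·C + γ·S + δ·C·S,

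with C = condition and S = time stratum. Moderation is δ. If δ is left out, then under 1:1 allocation within strata the coefficient of S estimates γ + δ/2. It mixes prognosis (γ) with half of the moderation (δ), and the two cannot be separated. Omitting condition as well does not change this expectation, because C is balanced within S.

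**Two scenarios (n = 132, equal strata, 4,000 simulated trials each).**

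| Scenario | γ | δ | γ + δ/2 | Time coefficient significant | Interaction significant |
|---|---|---|---|---|---|
| (a) 6-point effect in both strata, 4-point prognostic difference | 4 | 0 | 4 | 58-61% | about 5% |
| (b) effect 0 versus 12 points, opposing 6-point main effect of time | 6 | −12 | 0 | 3-4% | 93% |

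The ranges cover the model with and without condition.

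**Closed-form checks.**
- (a) SE of the time coefficient = 2 × 10.15 / √132 = 1.77; 4 / 1.77 = 2.26; power = Φ(2.26 − 1.96), about 62%. This agrees with the simulation.
- (b) SE of the interaction = 10.15 × √(4/66 + 4/66) = 3.53; 12 / 3.53 = 3.40; power = Φ(3.40 − 1.96), about 93%.

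**Second simulation (106 completers, SD 11, residual SD 10.26, equal strata, 3,000 trials).**
- A 6-point prognostic difference and no moderation: time coefficient significant in 84%, interaction in 5%.
- Effects of 0 versus 12 points with no average difference between strata: about 4% and 85%.
- With condition left out, the time coefficient is significant in 84% and 3%.

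**What the correct test can detect.** With p the share of patients in one stratum, SE = 10.15 × √[4/(pn) + 4/((1−p)n)].

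| n | Split | SE | Power for a 6-point interaction | Detectable with 80% power (2.80 × SE) |
|---|---|---|---|---|
| 132 | 50:50 | 3.53 | 40% | 9.9 points |
| 106 | 25:75 | 4.55 | 26% | 12.7 points |

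A more uneven split lowers this further. With SD 11, a 10:90 split gives power of about 15% (106 patients) to 17% (132 patients).

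**The case against.** Four points can be made for the plan.

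1. *The wording is elliptical.* The sentence just before names moderation, condition is a fixed factor in the other models, and the text for this aim may list only the covariates. The article never says that the time coefficient will be read as the moderation test. It is fair to assume that condition is implied. That does not rescue the model, which still lacks the product term and imposes a common effect.
2. *The analysis plan may specify the interaction.* It may, but this is not a detail left open. The article states a model, with its outcome and covariates, and that model does not match its aim.
3. *The scenarios are chosen.* This stands. The documents give no prognostic difference between strata, and the cited finding that fatigue does not fall further after 3 months points to a small one. With neither prognosis nor moderation, the time coefficient would be significant in only about 5% of trials. Scenario (b) is built so that the average difference cancels. The figures show that the two tests answer different questions, not how often an error would occur in this trial.
4. *It is the third of three aims.* This also stands. The primary and secondary ANCOVAs and the sample size are untouched. The eligibility limit of 3 months is already fixed and was chosen on cited findings, not on this analysis. A correct analysis remains possible after data collection, because the factor is stratified and recorded.

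**Conclusion.** The concern holds. The analysis stated for the third aim has no parameter for moderation, with or without condition in the model, under any SD and any split between strata. Its time coefficient estimates prognosis plus half of the interaction.

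The size of the possible error depends on assumptions that the article does not supply: an SD of about 10.9 inferred from the Power section, equal strata, and hypothetical prognostic and treatment effects. Under these the stated test rejects in 58-61% of trials without moderation and in 3-4% of trials with a 12-point moderation. The consequence is confined to the third aim. Even the correct test is weak: the interaction detectable with 80% power is about 10-13 points, against a main effect of 6 points that the trial was sized for.

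**What to change.** Replace the sentence on the third objective with a model that can answer it: ANCOVA of CIS-fatigue at T1 on CIS-fatigue at T0, condition, time stratum and condition × time stratum. State that the product term is the test of moderation, and report the treatment effect with a 95% CI in each time stratum. State also that a non-significant interaction will not be taken as evidence of equal effects, and preferably label the aim exploratory.

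Two smaller additions fit with this. Include the referral stratum, since it is the other stratification factor. Include the condition × time term in the imputation model used for this analysis, because imputing without it pulls the estimated interaction towards zero.

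The cost is a sentence or two of analysis wording. No new data, patients or assessments are needed.

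### The missing-data sensitivity analysis runs only after a significant result, so a non-significant result is never examined under other missing-data assumptions

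*Protocol article*

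**What the plan says.** All points are in the protocol article.

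- **Main method (Intended statistical analyses).** Analyses follow intention to treat. "Missing values on primary and secondary outcome measures will be replaced with multiple imputation", by fully conditional specification with at least five imputations. The variables in the imputation model are not listed, so it is not stated whether condition is one of them.
- **Sensitivity analysis (same section).** "In case of statistically significant differences, a sensitivity analysis will be performed, based on different assumptions about the values of missing data". The alternative assumptions are not named.
- **Expected loss (Power).** The margin is 19.5%, which is 1.5 times the 13% seen in an earlier trial of face-to-face CBT. The reason given is that "patients might experience less support from their therapist in the web-based CBT".
- **Follow-up (Procedure).** Outcomes are assessed at baseline (T0) and once more at 6 months (T1).

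**The concern.** Whether a robustness check is run should not depend on the p-value of the result it checks. Missing data can hide an effect as well as inflate one, and under this rule only the second possibility is ever looked at. If the imputation diluted a real effect into non-significance, the one check in the plan would not run.

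The setting makes this more than a formality. About one patient in five is budgeted as lost. The extra loss is explained by a feature of one arm's treatment, and no follow-up assessment before T1 is described that could inform the imputation. Drop-out related to outcome is therefore plausible in either arm, though the article does not assert it.

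**Working it through.** **1. Reproduce the plan's sample size.** Inputs from Power: "A clinically relevant difference of six points is expected for the primary outcome"; "alpha of 0.05, a two-sided significance level and a power of 0.85"; 60 per arm for a t-test; "the correlation of the baseline and outcome measure was 0.36"; drop-out 19.5%.

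- Design factor: 1 - 0.36² = 0.8704
- 60 x 0.8704 = 52.2, rounded up to 53 per arm
- 53 / (1 - 0.195) = 65.8, rounded up to 66 per arm, or 132 in total

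This matches the plan exactly.

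**2. Back-solve the SD (assumption).** No SD is given. With 60 per arm, a difference of 6, two-sided alpha 0.05 and power 0.85, the implied SD is 10.79 to 10.88 (t-test) or 10.97 (normal approximation). I use 10.88.

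**3. Standard error and significance limit with 53 evaluable per arm.**

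- ANCOVA SD: 10.88 x √0.8704 = 10.15
- SE: 10.15 x √(2/53) = 1.97
- Limit: 1.96 x 1.97 = 3.86 points (3.83 to 3.90 over the SD range)

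**4. No-benefit scenario.** Assume a 6-point effect in those observed, a proportion d missing at T1, and missing web-CBT patients who score like controls. The effect in all randomised patients is 6 x (1 - d).

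| d | effect (points) | 6 / effect | power, SE of 53 per arm |
|---|---|---|---|
| 0 (reference) | 6.00 | 1.00 | 0.86 |
| 0.13 | 5.22 | 1.15 | 0.75 |
| 0.195 | 4.83 | 1.24 | 0.69 |

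At 19.5% the shift is 6 - 4.83 = 1.17 points.

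**5. Simulation.** 1,500 trials, 66 per arm, true effect 6 points, 19.5% missing completely at random in each arm, 20 imputations.

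| imputation | mean effect | power |
|---|---|---|
| condition in the model | 6.03 | 0.85 |
| control-like for missing patients | 4.85 | 0.71 |
| condition left out of the model | 4.83 | 0.71 |

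The last row shows how imputation can dilute a real effect. Where that produces a non-significant result, the planned check is not triggered.

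**6. Which significant results are fragile?** Hold the SE at 1.97. An observed effect E becomes 0.805 x E under the no-benefit assumption and stays significant only if E exceeds 3.86 / 0.805 = 4.80. Observed effects of about 3.9 to 4.8 points could therefore lose significance. An observed 6 becomes 4.83 and stays above 3.86.

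**7. Tipping point.** Each CIS point by which missing patients in one arm are shifted moves the estimate by 0.195.

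- For an observed 6 points, significance is lost when missing web-CBT patients are (6 - 3.86) / 0.195 = about 11 points worse than imputed (10.8 to 11.1 over the SD range).
- The same arithmetic applies to a null result. For illustration, take an observed effect of half the planned difference, 3 points. It would become significant if missing web-CBT patients were (3.86 - 3) / 0.195 = 4.4 points better than imputed, or missing controls 4.4 points worse.

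**The case against.** In a superiority trial the main use of such an analysis is to stress-test a positive claim, and the plan does run it then. That stands, and it limits the point: the gap concerns null results. Control-based imputation, or worsening web-CBT scores, can only shrink the effect and would say little about a null result. This is why the shifts must go in both directions and cover both arms.

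Several stronger readings are tempting, and the document does not support them.

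- **That the main imputation credits drop-outs with completers' benefit.** The article does not say so. It depends on whether condition is in the imputation model: the simulation gives 6.03 with it and 4.83 without it.
- **That the alternative assumptions will be picked after the result is seen.** The article only leaves them unnamed, and a condensed article may leave such detail to the full protocol or SAP, which is not shown. Silence on this is not a defect in itself.
- **That drop-out reflects lack of benefit.** Power speaks of less therapist support, not less benefit, and applies the same 19.5% to both arms.
- **That 19.5% of T1 scores will be missing.** The figure is a planning margin. A patient who stops the modules but attends T1 keeps her observed score.
- **That missing data are the main threat to the estimate.** Nothing in the article supports ranking them above, for example, a self-reported outcome in a non-blinded trial with a waiting-list control.

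**Conclusion.** The point holds in a narrow form. The article states the significance trigger outright, so this is not an inference from silence, and its consequence is that a null result is never examined under other missing-data assumptions.

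The figure of 6.0 against 4.8 points is a scenario, not a forecast. It requires all 19.5% to lack T1 scores, condition to be in the imputation model, and no benefit in any missing web-CBT patient. A reader might take the ratio of 1.24 as a 24% bias built into the plan; the document does not support that. The significance limits also rest on the back-solved SD of about 10.9 and a constant SE. Under these assumptions a result at the planned 6 points is robust, and only observed effects of roughly 3.9 to 4.8 points are fragile. The change is a cheap improvement, not the repair of an error that undermines the primary analysis.

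**What to change.** In Intended statistical analyses:

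1. Delete the condition on significance and run the sensitivity analysis whatever the primary result.
2. State that condition is included in the imputation model.
3. Pre-specify control-based imputation of missing T1 scores in the web-CBT arm.
4. Pre-specify a delta-adjusted tipping-point analysis that shifts imputed scores in each arm separately and in both directions, and report the shift at which the conclusion changes. Extend the range until that happens. A range ending at 6 points would be too short, since an observed 6-point effect tips only near 11.

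The cost is a few lines of wording and slightly more analysis work. Sample size, visits and treatment are unaffected. The downside is that the sensitivity estimate may look less favourable than the primary one.
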